### Study setting

Proposed physical sites are high-risk foot services (HRFSs) of the following hospitals and a private podiatry clinic:Offloading clinic of Nepean Hospital, Nepean Blue Mountains Local Health DistrictSt Vincent’s Hospital Sydney, St Vincent’s and Mater Health NetworkWestern Sydney Podiatry, Penrith, NSW 2750

### Eligibility criteria

#### Inclusion criteria

Participants will be adults (≥18 years) with type 1 or type 2 diabetes, peripheral neuropathy and recently healed plantar forefoot ulcer. Participants must have at least one or more forefoot deformities such as claw/hammer toes, crossover toes, hallux valgus, hallux amputation, limited joint mobility, pes planus or pes cavus and bony prominences at metatarsal heads. Participants will have required a referral for orthopaedic footwear (either custom-made or prefabricated medical-grade footwear with or without modification) and custom-made insoles and have adequate English communication skills to comprehend the study procedures and provide informed consent.

#### Exclusion criteria

Exclusion criteria will be bilateral amputation (proximal to the trans-metatarsal joint), active or inactive Charcot foot, healed heel ulcers, midfoot deformities, use of walking aid for offloading the foot or severe illness, such that the participant may not survive the study period. Details are provided in the trial flow chart.

### Participant’s consent process

The participant will meet with the investigator prior to completing informed consent. The investigator will explain the rationale for the study, what participation will involve, follow-up requirements if applicable and any side effects or risks. Questions from the participant will be encouraged. The participant information sheet (PIS) will be provided and discussed with the participant. The participant may wish to consider their decision or discuss it with other parties, and in that case, another visit with the investigator can be arranged. The participants will be advised that they can withdraw from the study at any time without explanation or prejudice to future care. If willing, the participant will be asked to sign the informed consent form. The principal investigator for each site will sign the PIS after the participant has signed.

## Interventions

### Choice of comparisons

In this trial, participants’ existing footwear, insoles or offloading devices are the comparators. Participant’s current (standard) footwear, which may be regular retail shoes, orthopaedic footwear, post-op shoes or cam-walkers or moon boots with or without insoles (custom-made or prefabricated), will be used as the control arm for the trial.

### Intervention description

Footwear and insole are the interventions in this trial which are personalised and can be modified further to improve PPP offloading and increase adherence [39, 40]. Participants are required to select a preferred style of footwear and report on the activities for which they intend to wear the footwear. The choices of footwear are either prefabricated orthopaedic footwear with or without modification and fully custom-made orthopaedic footwear, which is made from individual foot measurements and 3D scans of the foot and leg. The insoles will be designed in response to foot assessment data, a foam impression box and a 3D scan of the individual foot. The insoles will be manufactured using conventional manufacturing or 3D printing method. Participants will be provided with instructions for wearing the footwear and insoles. The footwear and insole suitability for the participants will be carefully checked at the t1 appointment by the researcher and also by the referring podiatrist, which is part of the regular clinical protocol. This process will be continued during each visit to ensure they are suitable for the participant. The modification of footwear, insole and in-shoe plantar pressure measuring will continue until an acceptable pressure reduction is achieved and the participant is satisfied with them. In the unlikely event that an adverse effect is observed from the provided footwear and insole, the participant will be asked to stop using them until a further assessment is conducted by the researcher and the treating multidisciplinary team.

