In this proposed study, participants will have an initial assessment with the principal investigator, having been referred from the high-risk foot service. The initial assessment will include the selection of appropriate footwear, measuring, casting and 3D scanning of feet and technical specification of footwear and insole that reflects participant’s preferences. Barefoot static and dynamic pressure and in-shoe pressure measurements will be carried out. Current (standard) footwear, which may be a regular retail shoe, orthopaedic footwear, post-op shoes or cam-walkers or moon boots with or without insoles (custom or prefab), will be used as the control arm for the trial.

The second assessment will be done once the footwear and insole are ready for fitting (generally within 4 weeks after the initial assessment and measurement). In-shoe pressure analysis will be carried out in the new footwear and insole, which may undergo minor or major modification to achieve desired offloading efficacy. Participants will be assessed for walking comfort and satisfaction with their new footwear. Scores will be recorded on a Likert scale [59]. A third consultation will be arranged 2 weeks later. New footwear-wearing instructions will be provided to the participants, including contact details for an emergency or experiencing any adverse effect from the new footwear.

In the third assessment, the participant’s feet will be assessed for any redness or rubbing and any discomfort from the footwear. The participant’s self-reported wearing period data will be collected and analysed for wear patterns and frequency. The footwear will be assessed for any unusual wear marks or pressure points. Necessary adjustments will be made, and the fourth review session will be booked for a monthly visit.

During the fourth assessment, the participant’s feet and footwear will be assessed again. Participants’ satisfaction with the footwear will be recorded and compared with the participant’s self-reported wearing period data for the previous month. A similar process will follow, and another monthly appointment will be made with the researcher.

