In the fifth assessment, a similar process will follow as the previous review, and this is the endpoint of the study. Participants will be asked about the walking comfort and likeliness of footwear and suitability for the intended application. Overall feedback and any comments from the participants on the footwear will be recorded. Any repair or adjustments to the footwear and insoles will be carried out, and they will be given contact details for any future repair and follow-up reviews.

Double-blinding is not feasible in this study design, given the nature of the intervention and secondary outcomes. Blinding is recommended in N-of-1 trials, but it is not mandatory [52]. In this proposed study design, participants will need to be aware of the prescribed footwear in order to provide feedback on acceptance. Features of the footwear and insoles may be easily identifiable by clinicians in the team. However, the statistician will remain blinded, and this study design can be termed a single-blind trial [60, 61].

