### Outcomes

The primary outcome is a reduction of PPP at the accepted level according to the protocol (<200kPa or 30% reduction from the baseline/control) [64]. The outcome will be measured by using an in-shoe pressure analysis (F-Scan® system by Tekscan® [65]).

The participants will also undergo in-shoe plantar pressure measurements at each fitting and review appointment, where they need to walk up to 12 m at a self-selected pace that represents their regular pace of walking and is consistent during each measurement. F-Scan® sensors will be calibrated at ‘Walk’ calibration, and the body weight of the participant will be recorded each time during the analysis.

The secondary outcome is adherence (recorded from the participant’s self-report on the wearing period) and participant’s satisfaction with the provided footwear and insoles (in terms of walking convenience and aesthetics, to be measured by using a Likert scale [59]).

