### Accounting for potential bias, confounding factors and missing information

There is a potential risk of biasing the results for the researcher also being the treating clinician. However, the statistician will remain blinded to the condition of the participant. The participant will also remain de-identified to the statistician, including the footwear and insole design features prescribed to that specific participant. The study is non-randomised, and any missing data will be handled through ‘as treated’ analysis. The in-shoe plantar pressure measurement will be done by using the F-Scan® system by Tekscan® [65] and the F-Scan® research software 7.0. The software generates the pressure analysis report without the clinician’s intervention. The report is based on sensors calibration data and actual interaction of pressure between the foot, insole and footwear. Thus, the report remains independent of external influence to give a true reflection of the offloading efficacy of the footwear and insole’s design and subsequent modifications. Participant’s self-report on perceived clinical outcomes regarding plantar pressure offloading (<200kPa or 30% reduction from the baseline/control), suitability of the footwear and insoles and the review feedback from the treating podiatrists in the high-risk foot services will also reduce the risk of bias.

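### Measuring stops when the primary-outcome target is met, and nothing keeps that accepting reading out of the analysis; if it is analysed, offloading is overstated

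*Protocol article*

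**What the plan says.** All references are to the protocol article.

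- **Stopping rule (Intervention description).** Modification and "in-shoe plantar pressure measuring will continue until an acceptable pressure reduction is achieved and the participant is satisfied with them". No maximum number of attempts is stated.
- **Fitting visit (Methodological approach).** The new footwear is measured in-shoe and is something "which may undergo minor or major modification to achieve desired offloading efficacy".
- **Later visits (Methodological approach).** At the third assessment, "Necessary adjustments will be made, and the fourth review session will be booked for a monthly visit". The fourth and fifth follow a similar process. At the fifth, which is called the study endpoint, "Any repair or adjustments to the footwear and insoles will be carried out".
- **Primary outcome (Outcomes).** "The primary outcome is a reduction of PPP at the accepted level according to the protocol (<200kPa or 30% reduction from the baseline/control"). On the instrument: "The outcome will be measured by using an in-shoe pressure analysis", using F-Scan. On timing: "The participants will also undergo in-shoe plantar pressure measurements at each fitting and review appointment".
- **Control (Rationale for control).** In-shoe measurements in the participant's existing footwear form the baseline. No rule for repeating them until some value is reached is stated.
- **Analysis (Data analysis).** A paired t-test compares plantar pressure in the new footwear with the control footwear. Which of the t1 to t4 readings enters is not stated.
- **Safeguard (Accounting for potential bias, confounding factors and missing information).** The software produces the report without the clinician. "Thus, the report remains independent of external influence to give a true reflection of the offloading efficacy".

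**The concern.** The criterion that ends a round of modification is, on a natural reading, the criterion that defines primary-outcome success, and both use in-shoe F-Scan. A reading that ends a round has been picked because it passed. Some of that pass is true offloading and some is favourable measurement error. The control readings are not picked in this way, so the error does not cancel in the paired difference.

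The person who decides when to stop is the researcher, who is also the treating clinician and sees the readings. Automatic report generation protects each reading; it does not protect the choice of which reading is the last. A blinded statistician cannot undo a selection that is already in the data.

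At stake are both summaries of the primary outcome: the share of participants reaching the accepted level, and the mean reduction in the paired t-test. The prescribing algorithm that the trial is meant to deliver would rest on them.

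**Working it through.** The article gives no effect size, standard deviation or repeatability for PPP, and the 21 participants do not come from a calculation. There is no stated figure to reproduce, so the check is of the measurement rule itself.

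**Step 1. Logic.** A round that ends under the stated rule ends on an acceptable reading. If *acceptable* there means the accepted level in Outcomes, every completed round scores as a success at its closing reading, whatever the true offloading. Failures can come only from participants who never complete a round.

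**Step 2. Inputs for an illustration.** From the article: the 30% reduction criterion. Assumed, because the article does not give them:
- log-normal noise on the control reading and on each new-footwear reading, with CV 5%, 10% or 15%;
- a true reduction of 20%;
- modifications that add nothing;
- at most five readings, stopping at the first that is no more than 0.70 × the control reading.

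The <200 kPa criterion is not modelled.

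**Step 3. One reading only.** With σ = √ln(1 + CV²), the chance of an apparent 30% reduction is Φ[ln(0.70/0.80) / (σ√2)], and ln(0.875) = −0.1335.
- CV 5%: σ = 0.0500, z = −1.89, chance 3%.
- CV 10%: σ = 0.0998, z = −0.95, chance 17%.
- CV 15%: σ = 0.1492, z = −0.63, chance 26%.

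**Step 4. Stop at target, up to five readings (simulation).** All attempts share one control reading and so are not independent. At 10% CV the formula 1 − (1 − 0.172)⁵ = 0.61 would overstate the chance of a pass, and simulation is needed.

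| CV | Success, 1 reading | Success, up to 5 | Mean recorded reduction (ratio of means) | Truth |
|---|---|---|---|---|
| 5% | 3% | 10% | 20.6% | 20% |
| 10% | 17% | 44% | 23.7% | 20% |
| 15% | 26% | 59% | about 26.5% | 20% |

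A fresh reading of the same footwear returns a mean of 20% and the one-reading success rate.

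**Step 5. How far this depends on the assumptions.**
- *Truth well beyond the threshold.* With a true reduction of 40% and 10% CV, the recorded mean is about 41%.
- *Modifications that work.* Starting at 20%, gaining 5 points per modification, 10% CV: the recorded mean is about 35% against a true mean of 30.2%. Of the 15-point rise, about 10 points (two-thirds) are real and about 5 are selected noise.
- *Noise placed directly on the reduction, independent at each attempt, SD 10 points.* With truth 20%, success goes from 16% to 58% and the recorded mean is 27.6%.
- *Paired t-test with zero true effect, n = 21, up to five attempts, same noise model.* Two-sided type I error is 0.05, 0.05, 0.11 and 0.38 at SD 5, 10, 15 and 20 points.

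**The case against.** The strongest reply is that the article never says the accepting reading is the one analysed. Pressure is collected at every fitting and review, the fifth assessment is called the endpoint, and the choice of reading could sit in the full protocol or the analysis plan. If the analysed value is a t4 reading taken before any adjustment, the selection largely disappears. This stands, and it makes the point conditional. It does not remove it: the article fixes a stop-at-target rule and claims that the resulting report truly reflects offloading efficacy, while leaving the selected reading eligible.

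Several stronger readings are tempting, and the article does not support them.

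- *Success is guaranteed by construction.* Stopping also requires that the participant is satisfied, so modification may continue past a passing reading. Some participants may never reach the target or may withdraw. Equating the acceptable reduction with the threshold in Outcomes is reasonable, but it is an inference.
- *The control is one unrepeated reading.* The article speaks of baseline measurements in the plural and gives no number. Only the absence of a repeat-until-target rule is supported.
- *The t4 reading is contaminated by adjustments at that visit.* Those adjustments are listed after the review and feedback and read as close-out servicing. The article does not say that pressure is measured again afterwards.
- *The trial cannot tell offloading from repeated measuring.* Modifying to target is the intervention, so part of the gain at acceptance is real. With low noise or a large true reduction the bias in the mean is slight, and the t-test's type I error is inflated only when noise is large.

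**Conclusion.** The point holds in conditional form. If the reading that closed a modification round is analysed, the success proportion is largely uninformative and the mean reduction is biased upward. The article neither says that this reading is used nor rules it out.

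The size is unknown, because it turns on F-Scan repeatability and the number of attempts. Under the illustrative assumptions (30% criterion only, true reduction 20%, no real gain from modification, up to five readings), the success rate is multiplied by two to three and a half, and the mean is overstated by about half a point to six and a half points. These figures show how the mechanism behaves; they do not estimate what happened in this trial.

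The statement that the report is independent of external influence is true at most of how a single reading is generated. It does not cover the decision to stop measuring.

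**What to change.** Leave the clinical modification process as it is and fix which reading is analysed.

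1. Define the primary PPP as one pre-specified reading that did not close a modification round. One example is the t4 arrival reading, taken in the footwear as worn and before any adjustment that day. Use it for both the success proportion and the paired t-test.
2. Report descriptively the first t1 reading (before modification), the accepted t1 reading and the number of modifications.
3. Use arrival readings at t2 and t3 for any analysis over time.
4. Limit the claim of independence from external influence to the generation of each individual reading.

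**Cost.** Wording in the protocol or analysis plan, and a before/after-adjustment flag on the case report form. In-shoe pressure is already due at each visit, so no visit is added. Recruitment has started at two centres, so for participants already measured the order of readings must be recoverable from existing records. The reported success rate will probably be lower. A t4 reading also answers a somewhat different question: offloading after about ten weeks of wear (2 + 4 + 4) and not at fitting. If offloading at fitting is wanted, an independent re-measurement after acceptance at t1 would also remove the selection, at the price of one extra reading.

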### Strategies to improve adherence to interventions

The interventions in this trial are therapeutic footwear and insole that are personalised and can be modified further when needed. These are wearable items of clothing for the participant. Participants’ preferences and the suitability of use will be considered in the selection of footwear interventions. There will be regular follow-up with participants, and participants’ self-reported data on adherence and satisfaction with the footwear and insole will be collected at each appointment. Participants will be given the motivation to adhere to the therapies by the researcher and other research team members, including explanations of the benefits of the devices and the adherence.

### Provisions for post-trial care

These participants are at high risk of foot re-ulceration and are advised to be under regular podiatry care either at the community health clinics or their private podiatry clinics. They are also advised to visit the nearest high-risk foot services for any unlikely incident with their feet, such as an active wound or infection, with a referral from their GP or via the emergency department of the respective hospital. Participants will be advised to undergo twelve-weekly reviews with their pedorthists to ensure the footwear and insoles are repaired and optimally maintained.

### Outcomes

The primary outcome is a reduction of PPP at the accepted level according to the protocol (<200kPa or 30% reduction from the baseline/control) [64]. The outcome will be measured by using an in-shoe pressure analysis (F-Scan® system by Tekscan® [65]).

The participants will also undergo in-shoe plantar pressure measurements at each fitting and review appointment, where they need to walk up to 12 m at a self-selected pace that represents their regular pace of walking and is consistent during each measurement. F-Scan® sensors will be calibrated at ‘Walk’ calibration, and the body weight of the participant will be recorded each time during the analysis.

The secondary outcome is adherence (recorded from the participant’s self-report on the wearing period) and participant’s satisfaction with the provided footwear and insoles (in terms of walking convenience and aesthetics, to be measured by using a Likert scale [59]).

### Participant timeline

This project will last between 3 and 4 months, including the initial assessment, fitting of footwear and insoles and then at least three reviews outlined in the trial design flowchart in Fig. 1. The details of the timelines are t0, initial consultation; t1, 1st fitting appointment after the initial consultation; t2, 2-week review from fitting appointment; t3, 4 weeks from the 2nd review appointment; and t4, 4-week review from the 3rd review appointment.

### Sample size

Twenty-one participants [51] from the HRFSs of two major public hospitals and their affiliated community clinics (Nepean Hospital, St Vincent’s Hospital Sydney) and a private podiatry clinic (Western Sydney Podiatry) in Sydney will be recruited for the study. A sample size calculation is not possible due to the non-existence of a well-validated Quality of Life Scale (QOLS) for the target population. The QOLS measures an individual’s satisfaction, perceptions of control, involvement, commitment and work-life balance regarding an individual’s personal perception. Previous studies [51, 66–68] utilising the N-of-1 methodology have recruited between 10 and 25 participants.

### Recruitment

Participants will be recruited from the aforementioned HRFSs and the private podiatry clinic. Potential participants will be identified by interdisciplinary team members of the HRFSs, including endocrinologists, pedorthists and podiatrists. Participants will then be invited to participate.

### Accounting for potential bias, confounding factors and missing information

There is a potential risk of biasing the results for the researcher also being the treating clinician. However, the statistician will remain blinded to the condition of the participant. The participant will also remain de-identified to the statistician, including the footwear and insole design features prescribed to that specific participant. The study is non-randomised, and any missing data will be handled through ‘as treated’ analysis. The in-shoe plantar pressure measurement will be done by using the F-Scan® system by Tekscan® [65] and the F-Scan® research software 7.0. The software generates the pressure analysis report without the clinician’s intervention. The report is based on sensors calibration data and actual interaction of pressure between the foot, insole and footwear. Thus, the report remains independent of external influence to give a true reflection of the offloading efficacy of the footwear and insole’s design and subsequent modifications. Participant’s self-report on perceived clinical outcomes regarding plantar pressure offloading (<200kPa or 30% reduction from the baseline/control), suitability of the footwear and insoles and the review feedback from the treating podiatrists in the high-risk foot services will also reduce the risk of bias.

